### Intervention

#### Intervention group

Subjects in the intervention group will be treated with auricular acupressure for 12 months. The product used for auricular acupressure is Wangbuliuxingzi (vaccaria seed) auricular adhesives (Shanghai Taicheng Science and Technology Development Co., Ltd., registration No. Huxuxiebei 20160002), and the product information is shown in Figure S2. According to the clinical experience of our research group and the effective prescription published before [20, 33], six acupoints [eye (LO_5_), liver (CO_12_), kidney (CO_10_), heart (CO_15_), spleen (CO_13_), and shenmen (TF_4_)] will be selected as the auricular acupoint protocol in this study. The localization of the acupoints refers the Nomenclature and Location of Auricular Acupoints [34] stipulated by the World Federation of Acupuncture-Moxibustion Societies (WFAS) in 2013. The anatomical locations are listed in Table 2 and illustrated in Figure S3.

**Table 2 Tab2:** Location of the auricular acupoints

Acupoint	Location
Eye (LO_5_)	In the center of the anterolateral surface of the ear lobe
Liver (CO_12_)	In the posteroinferior part of the cymba conchae
Kidney (CO_10_)	In the cymba conchae below the posterior region of the inferior antihelix crus
Heart (CO_15_)	In the center of the depression of the cavum conchae
Spleen (CO_13_)	In the posterior upper part of concha cavity
Shenmen (TF_4_)	In the upper part of the posterior 1/3 of the triangular fossa

Operation is as follows: After standard sterilization for the auricular acupoints with 75% alcohol, the auricular adhesives are attached to the acupoints with the pellets precisely targeting the acupoints, eye (LO_5_), liver (CO_12_), kidney (CO_10_), heart (CO_15_), spleen (CO_13_), and shenmen (TF_4_), and pressed tightly. This process will be operated by professional acupuncturists after unified training. The guardian is asked to press the adhesives once every day in the morning (6:30 am–7:30 am), after school (4:00 pm–5:00 pm), and before bed time (9:00 pm–10:00 pm). A good adherence is defined as “completing at least 5 times of acupressure operation during two consecutive days (required to do 3 times a day)”. Each acupoint should be pressed 20 times each session, and the press should be causing distending and aching sensation but within the kid’s tolerance. Every night, the guardian should record the completion status in the diary card, and send the diary card photos to the researcher through WeChat every week. One ear is treated each time (to be alternately at each visit), and the auricular adhesives are changed by the acupuncturist each week. Since the adhesives may fall off due to exercise, bathing and other unexpected conditions, the researcher would send the auricular acupoint atlas and the video on auricular point sticking to the guardian after recruitment, so as to guide the guardian to re-apply the plaster to the original spot after the adhesive falls off. If skin abrasion or swelling occurs at the treated spots during, the guardian needs to contact the acupuncturist immediately to deal with it, which will be recorded in the case report form (CRF).

#### Control group

The subjects in the control group will not receive any interventions for myopia prevention or control within 12 months, but only go to the hospital to check the relevant optical indicators at the required time points.

### Outcome observation

Subjects in both intervention group and control group will be measured for SE, axial length, uncorrected visual acuity, retinal, and choroidal thickness at baseline, and 3, 6, 9, and 12 months after recruitment. All the researchers involved in data evaluation were trained strictly before the start of the trial.

#### Primary outcome measures

The primary outcome measures include MI and SE.

The measurement of SE will be carried out with Nidek ARK-1 refractometer produced by Nidek, Japan. Before measurement, the subjects were given one drop of 0.5% proparacaine hydrochloride eye drops (Alcaine), one drop of 1% cyclopentolate hydrochloride eye drops (CYCLOGYL) 1 min later, and one drop of 1% cyclopentolate hydrochloride eye drops (CYCLOGYL) 5 min later, to induce cycloplegia, getting ready for automatic optometry 30 min later. The measurement will be performed three times successively. Make sure that the maximum-minimum difference in the spherical and cylindrical diopters should be no more than 0.25 D, respectively, and the average value of the three measurement results will be recorded. The SE is defined as spherical diopter plus 1/2 cylindrical diopter. According to existing reports and clinical routines [35], we define myopia as SE ≤ − 0.50 D.

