**Method/design:**

A total of 480 subjects at 8–9 years old will be randomized in a 1:1 ratio to an intervention group versus a control group. The intervention group will receive auricular acupressure for 12 months, while the control group will be taken as a blank control. The primary and secondary outcomes will be measured at baseline, and again at 3, 6, 9, and 12 months after recruitment. The myopia incidence (spherical equivalent ≤ − 0.50 D) and the mean change of spherical equivalent will be taken as the primary variables; the secondary outcome measures include axial length, uncorrected visual acuity, and choroidal and retinal thickness.

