#### Sample size

So far, there is no high-quality randomized controlled trial (RCT) studying the sole use of auricular acupoints in reducing the MI. Increasing outdoor time is the main method well recognized in the prevention of myopia. Therefore, the preventive effect of outdoor activities is used to estimate the efficacy of auricular acupoints. The MI in the intervention group 8.41%/year, and that in the control group is 17.65%/year [32]. When we set α = 0.05, test efficiency 1 – β = 0.80, and the ratio between the two groups 1:1, the calculated required sample size is 204 for each group according to the following equation, that is 408 in total. Then, when the dropout is set at 15% or less, a total of 480 participants should be recruited in this study.
$$ n=\frac{{\left({\mathrm{Z}}_{1-\alpha }+{\mathrm{Z}}_{1-\beta}\right)}^2}{{\left({\pi}_r-{\pi}_c\right)}^2}\left[{\pi}_r\left(1-{\pi}_r\right)+{\pi}_c\left(1-{\pi}_c\right)\right] $$$$ {\pi}_r= MI\ \mathrm{in}\ \mathrm{the}\ \mathrm{intervention}\ \mathrm{group} $$$$ {\pi}_c= MI\ \mathrm{in}\ \mathrm{the}\ \mathrm{control}\ \mathrm{group} $$

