### Statistical analysis

SPSS version 25.0 will be used for data processing in this trial. Only ocular parameters of the right eye will be included for statistical analysis. Analyses will be performed based on a modified intention-to-treat principle and involve only subjects who have both a baseline outcome measurement and at least one post-randomization observation. Last-observation-carried-forward approach will be used to replace missing data.

The measurement data will be expressed as means ± standard deviation or median (interquartile interval), and the counting data will be described by the number of cases (percentage). Fisher’s exact test or Pearson’s chi-square test will be used for trial group comparisons of 1-year cumulative MI. Generalized estimating equations (GEE), with one within-subject factor (time), one between-subject factor (intervention), and their interactions, will be used to compare changes in spherical equivalent, axial length, uncorrected visual acuity, and choroidal and retinal thickness. The covariates in the GEE models include the corresponding baseline measures, age, gender, number of myopic parents, outdoor light exposure time, and near-work time. All the tests of effects will be conducted at a two-sided alpha level of 0.05.

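### MI and SE change are both primary at the full two-sided 0.05, with no order, win rule or deciding SE contrast; if either may count as success, the chance of a false primary result is up to 9.75%, and more if the SE contrast is chosen afterwards.

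*Protocol article*

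**What the plan says.** - **Two primary outcomes.** Under Primary outcome measures: "The primary outcome measures include MI and SE". The abstract also lists two, MI and SE change: "the mean change of spherical equivalent will be taken as the primary variables".
- **One alpha for every test.** Statistical analysis: "All the tests of effects will be conducted at a two-sided alpha level of 0.05".
- **MI has a fixed time point and test.** "Fisher’s exact test or Pearson’s chi-square test will be used for trial group comparisons of 1-year cumulative MI".
- **SE has a model but no deciding result.** GEE, "with one within-subject factor (time), one between-subject factor (intervention), and their interactions, will be used to compare changes in spherical equivalent". The abstract gives the visits: "The primary and secondary outcomes will be measured at baseline, and again at 3, 6, 9, and 12 months after recruitment". No visit, average or interaction term is named as the primary SE comparison.
- **The sample size rests on MI.** "The MI in the intervention group 8.41%/year, and that in the control group is 17.65%/year", with alpha 0.05, power 0.80, 204 per group and 480 in total after 15% dropout.
- **The two outcomes are linked.** MI is SE cut at a threshold: "we define myopia as SE ≤ − 0.50 D".

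The article gives no order of testing, no split of alpha and no rule on whether one or both outcomes must be positive.

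**The concern.** Two primary tests at the full 0.05 keep the overall error at 5% only if a rule links them, such as a fixed order or a requirement that both succeed. Without a rule, a significant result on either outcome could be presented as a positive trial, and the overall error would exceed the stated 0.05.

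The open SE comparison adds to this. With four post-baseline visits and a model holding time, arm and their interaction, the SE result could be the month-12 difference, an earlier visit, the average arm effect or the interaction. Unless one is fixed beforehand, the choice can follow the data.

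At stake is whether a claim that auricular acupressure prevents or slows myopia carries the error rate that the protocol attaches to it.

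**Working it through.** **1. The plan's own figure.** Inputs from Sample size: 8.41% and 17.65%, alpha 0.05, power 0.80, 1:1.

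Variance term: 0.0841 × 0.9159 + 0.1765 × 0.8235 = 0.22237. Difference: 0.0924; squared, 0.008538.

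n = (1.960 + 0.842)² × 0.22237 / 0.008538 = 7.849 × 26.046 = 204.4 per group, against 204 stated. Then 408 / 0.85 = 480. The figure reproduces with the two-sided z value, so the whole two-sided 0.05 is spent on MI. (The printed formula has Z with subscript 1 − α; read literally as one-sided it gives 161.)

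**2. Two tests at 0.05, either may count, one SE test.** If all effects are null and the two statistics are bivariate normal with correlation ρ, the chance of a false primary result is P(|Z₁| > 1.96 or |Z₂| > 1.96). At ρ = 0 this is 1 − 0.95² = 9.75%, the maximum. The last column counts only false results in favour of the intervention, for which one test alone gives 2.5%.

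| Assumed ρ | Either significant, two-sided | Either significant, benefit only |
|---|---|---|
| 0 | 9.75% | 4.9% |
| 0.4 | 9.3% | 4.7% |
| 0.5 | 9.1% | 4.5% |
| 0.6 | 8.75% | 4.4% |
| 0.7 | 8.35% | 4.2% |
| 0.75 | 8.1% | 4.05% |
| 0.8 | 7.8% | 3.9% |

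**3. Which correlation is plausible?** The protocol gives none, so this is an assumption. Two guides:

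- Cutting a normal variable so that a fraction p lies beyond the cut gives correlation φ(z_p) / √(p(1 − p)) between the variable and its dichotomy. At p = 0.0841 this is 0.56 and at p = 0.1765 it is 0.68. The false-positive chance is then 8.9% and 8.4%.
- A null simulation used 204 per arm and four visits. MI was SE at or below −0.50 D at any visit, tested without adjustment; the SE visit and average tests were adjusted for baseline. Four settings were run, 8,000 trials each, with assumed mean SE change of −0.05 to −0.2 D per year, SD of change 0.3–0.4 D and measurement error SD 0.10–0.12 D. The correlation was 0.45–0.56 in size, and the chance of a false result on MI or a single SE test was 9.0–9.5%.

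Together these support about 8–9.5% for correlations of roughly 0.4–0.75.

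**4. If the SE comparison stays open.** The same simulation gave:

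- MI, SE average arm effect or interaction: about 13%.
- MI or SE at any of the four visits: about 16–18%.

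These depend on the assumed SE changes and show direction and rough size only.

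**5. If both must succeed.** The chance cannot exceed that of either test alone, so it is at most 5%.

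**6. Cost of the remedies for MI power at 204 per arm.** The standardised difference is 0.0924 / √(0.22237 / 204) = 0.0924 / 0.03302 = 2.799.

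- Alpha 0.05: Φ(2.799 − 1.960) = 79.9% (79.4% with pooled variance under the null).
- Alpha 0.025: Φ(2.799 − 2.241) = 71.1% (70.4% pooled). Restoring 80% would need 248 per group, and 496 / 0.85 gives 584 in total.
- Fixed order with MI first: MI is still tested at 0.05, so its power is unchanged.

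**The case against.** The strongest reply is that this is mostly absence. The article is condensed, the analysis plan is not shown, and an order of testing, a win rule and the deciding contrast of a repeated-measures model are often set there. The alpha sentence is also compatible with a fixed order or a both-must-succeed rule, since each would run both tests at 0.05.

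Part of this stands: the protocol does not say that either outcome suffices, so an inflated error rate is a consequence of one reading and not a stated fact. The reply does not dispose of the point, because the protocol is not silent. It names two primaries and gives every test the full 0.05. Which outcome decides the trial, and when it is measured, is core protocol content. Followed as written, the rule does not protect the primary claim.

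A second reply is that onset (MI) and progression (SE) are separate aims, each entitled to its own 5%. That position is arguable, but the protocol does not take it. It would also leave the SE visit and contrast open.

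Third, a both-must-succeed rule or another multiple-testing procedure would also hold 5%. That is correct. The order proposed under the fix is one adequate choice, preferred because the sample size was built on MI.

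**Conclusion.** The point holds in conditional form. Two primaries are each tested at two-sided 0.05 with no order, no win rule and no deciding SE visit or contrast. If either may count and SE gives one test, the chance of at least one false significant primary result is at most 9.75%, and about 8–9.5% for assumed correlations of roughly 0.4–0.75. For false claims of benefit alone it is about 4.2–4.7% (correlation 0.7 down to 0.4) against 2.5%. It rises if the SE comparison is chosen after seeing the data, and is at most 5% if both outcomes must succeed.

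Three stronger readings are not supported:

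- A reader might infer that the trial's error rate simply is 8–9%. That needs an either-wins rule, a single SE test and a correlation of about 0.5–0.75, none of which the protocol gives. It also leaves out the effect of the open SE comparison.
- A reader might infer that sizing the trial on MI alone is an error. It is not: the protocol says openly that it did so and claims no power for SE.
- A reader might extend the point to the regional choroidal and retinal thicknesses. These are secondary outcomes, and this finding does not rest on them.

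**What to change.** Before any results are known, state in the outcome and statistics sections that:

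1. One-year cumulative MI, on which the sample size is built, is tested first at two-sided 0.05.
2. The month-12 arm contrast in SE change from the GEE is tested second, at two-sided 0.05, and only if MI is significant.
3. SE at months 3, 6 and 9 and the arm-by-time interaction are supportive.

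SE can then be declared significant only after MI has passed, so the chance of any false primary result across these two tests is at most 5%. The change is wording only: 204 per arm and 480 in total stand, and MI keeps about 80% power. The downside is that SE alone cannot carry a confirmatory claim if MI fails.

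If the sponsor wants SE on an equal footing, a both-must-succeed rule also holds 5%, but its overall power cannot exceed that of MI and depends on SE power, which is not stated. Using 0.025 for each lets either outcome win, at the price of MI power of about 70–71% or a total of 584.

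This covers the two final tests only. The interim analysis of the main indicators described under Trial monitoring is a further look at the data, which this wording does not address.

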#### Secondary outcome measures

The secondary outcome measures include the eye’s axial length, uncorrected visual acuity, and choroidal and retinal thickness.

Measure the axial length using IOL-Master (Carl Zeiss, Germany): Make sure the examinee takes a comfortable position. Adjust the height of the instrument according to the height of the examinee, and instruct him/her to fix the mandible and forehead on the jaw and frontal brackets, and adjust the eyes’ position. Ask the examinee to keep their eyes still by looking at the fixation lamp. The axial length will be measured three times and the mean value will be obtained.

The uncorrected visual acuity will be tested using the international standard visual acuity examination charm at a 5-m distance under the same lighting condition. From the optotype 4.0, move down line by line if the participant can see it clearly; if not, then check upward line by line. The participant will be given maximum 5 s to identify each optotype. From the line 4.0 to 4.5, move up one line when one optotype in the same line is misread; from line 4.6 to 5.0, two misreads allowable; from line 5.1 to 5.3, the number is three. The best visual acuity will be recorded if the participant successfully tells all the optotypes; if not, the final visual acuity will be considered the last line successfully identified. The results will be converted into Log-MAR for statistical analysis.

Measure the choroidal and retinal thickness using optical coherence tomography (OCT, RS-3000; NIDEK, Japan): Prior to OCT examination, the examiner should describe the examination process and precautions to the subject, and start the examination after obtaining the consent. The examinee stays in a sitting position. Adjust the height of the instrument according to the height of the examinee, and instruct the subject to fix the mandible and forehead on the brackets, and adjust the eyes’ position. The retina will be scanned in a cross-sectional manner in the range of 6 mm × 6 mm with macular fixation module, and the scanning center coincides with the fovea. The OCT built-in software program automatically detects and displays layers of retinal and choroid. Each layer is divided into three concentric circles: 1 mm central fovea, 1–3 mm parafovea, and 3–6 mm perifovea. The parafovea and perifovea can be further divided into 4 regions: upper, lower, nasal, and temporal. So there are a total of nine regions to measure the thickness of retina and choroid.

### Data collection and management

The collection of all baseline data and general information of each subject will be completed within 1 week before the start of the intervention. The general data include gender, age, school grade, number of myopic parents, past history, and medication history. The baseline data include spherical equivalent, axial length, uncorrected visual acuity, corneal curvature, and choroidal and retinal thickness. At 3, 6, 9, and 12 months after recruitment, the SE, axial length, uncorrected visual acuity, and choroidal and retinal thickness will be measured again to observe the changes. The data collection timeline is shown in Figure S4.

The information of each subject will be recorded in the CRF and the electronic database ResMan, with codes and abbreviations used instead of their names to protect privacy. The data in CRF form and ResMan will be independently input and checked by two third-party data administrators unrelated to the test to ensure the accuracy. If the subject requests to withdraw from the trial, the eye condition of the subject will be evaluated as quickly as possible. For suspicious data, the data manager will conduct data recheck query (DRQ) and give feedback to the researcher. The researcher should reply as soon as possible for the doubtful data, and the data manager will modify, confirm, and input the data according to the researcher’s reply. All paper and electronic documents will be kept, and the data printed on thermal paper will be photographed. Therefore, if readers or reviewers have any questions, they can certainly contact the authors for the original data.

### Statistical analysis

SPSS version 25.0 will be used for data processing in this trial. Only ocular parameters of the right eye will be included for statistical analysis. Analyses will be performed based on a modified intention-to-treat principle and involve only subjects who have both a baseline outcome measurement and at least one post-randomization observation. Last-observation-carried-forward approach will be used to replace missing data.

The measurement data will be expressed as means ± standard deviation or median (interquartile interval), and the counting data will be described by the number of cases (percentage). Fisher’s exact test or Pearson’s chi-square test will be used for trial group comparisons of 1-year cumulative MI. Generalized estimating equations (GEE), with one within-subject factor (time), one between-subject factor (intervention), and their interactions, will be used to compare changes in spherical equivalent, axial length, uncorrected visual acuity, and choroidal and retinal thickness. The covariates in the GEE models include the corresponding baseline measures, age, gender, number of myopic parents, outdoor light exposure time, and near-work time. All the tests of effects will be conducted at a two-sided alpha level of 0.05.

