#### Elimination criteria

Those who do not meet the inclusion criteria or match the exclusion criteria but were mistakenly included and have no post-randomization observation.

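### The analysis set depends on having an observation after open-label allocation; contact differs by arm, so the children analysed need not be those randomised, with a bias of uncertain direction

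*Protocol article*

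**What the plan says.** The Statistical analysis section adopts a modified intention-to-treat principle. Analyses will "involve only subjects who have both a baseline outcome measurement and at least one post-randomization observation", and "Last-observation-carried-forward approach will be used to replace missing data". The Elimination criteria use the same term for children enrolled in error who "have no post-randomization observation". Neither section defines an observation.

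The following sections bear on how a child comes to have one:

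- **Blinding:** examiners, data processors and statisticians are blinded; subjects and those delivering the intervention are not.
- **Intervention group:** "the auricular adhesives are changed by the acupuncturist each week", and guardians send diary photographs every week.
- **Control group:** these children "only go to the hospital to check the relevant optical indicators at the required time points". In Table 1 the first such point after allocation is month 3.
- **Outcome observation:** the measurement schedule is common to both arms: "Subjects in both intervention group and control group will be measured for SE, axial length, uncorrected visual acuity, retinal, and choroidal thickness at baseline". Later measurements follow at months 3, 6, 9 and 12.
- **Data collection and management:** "If the subject requests to withdraw from the trial, the eye condition of the subject will be evaluated as quickly as possible". This is not limited to one arm.
- **Dropout criteria:** two kinds of dropout are recognised, those who ask to leave and those who do not ask but fail to complete.

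**The concern.** Membership of the analysis set is decided by something that happens after allocation is known to the family. If the chance of that event differs between arms, randomisation no longer protects the comparison.

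Outcome examinations are scheduled at the same months in both arms, so the route to a difference is the child who leaves before month 3. Such a child enters the set only if examined at exit, and the prescribed exit evaluation follows a request to withdraw. A treated family in weekly contact has frequent occasions to make that request and to be brought in for it. A control family has no scheduled contact until month 3 and may simply not attend, which triggers no evaluation. Early leavers could therefore be kept more often in the treated arm.

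This affects a primary outcome in two ways. A retained early leaver contributes an early, almost always non-myopic value, which LOCF turns into a 12-month result. An excluded early leaver drops out of the denominator, which matters if leavers differ in risk from those who stay.

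**Working it through.** **1. The plan's own figures.** Sample size gives myopia incidence of 8.41% (intervention) and 17.65% (control), 80% power and α = 0.05. With two-sided α, the printed formula gives n = (1.960 + 0.842)² × [0.0841 × 0.9159 + 0.1765 × 0.8235] / 0.0924² = 204.4 per group. This agrees with the stated 204, and 408 / 0.85 = 480. The planned difference is 17.65 − 8.41 = 9.24 points, with 240 randomised per arm. None of this is disputed.

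**2. Assumptions not in the article.** Let f be the share of each arm leaving before month 3, taken as 5–15%. The upper end is the dropout allowance for the whole study, so placing all of it before month 3 is extreme. Let e be the share of those leavers examined at exit. Leavers are taken to be at average risk and non-myopic at exit.

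**3. Retention combined with LOCF.** Set the true incidence to p = 17.65% in both arms, so there is no effect. The incidence shown is p(1 − f) / [(1 − f) + f·e]. For f = 10% and e = 0.8, it is 0.15885 / 0.98 = 16.21%. For e = 0.2, it is 0.15885 / 0.92 = 17.27%. The difference is 1.06 points in favour of treatment. The type I error below is a normal approximation for the two-proportion test, with 240 randomised per arm and a nominal 5%.

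| e, treated vs control | f | Shown, treated | Shown, control | Spurious benefit (points) | Type I error |
|---|---|---|---|---|---|
| 0.8 vs 0.2 | 5% | 16.94% | 17.47% | 0.53 | 5.3% |
| 0.8 vs 0.2 | 10% | 16.21% | 17.27% | 1.06 | 6.1% |
| 0.8 vs 0.2 | 15% | 15.47% | 17.05% | 1.58 | 7.4% |
| 1 vs 0 (bound) | 5% | 16.77% | 17.65% | 0.88 | 5.8% |
| 1 vs 0 (bound) | 10% | 15.88% | 17.65% | 1.76 | 8.0% |
| 1 vs 0 (bound) | 15% | 15.00% | 17.65% | 2.65 | 11.9% |

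At 0.6 vs 0.3 the spurious benefit is 0.27, 0.53 and 0.80 points. With equal e in both arms it is zero.

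**4. Exclusion alone.** Assume 10% of controls and 3% of treated children are dropped, at r times the average risk of their arm. The incidence shown is (p − f·p·r) / (1 − f).

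- r = 1.5: control 0.1765 × 0.85 / 0.90 = 16.67%; treated 0.0841 × 0.955 / 0.97 = 8.28%; difference 8.39 points.
- r = 2: control 0.1765 × 0.80 / 0.90 = 15.69%; treated 0.0841 × 0.94 / 0.97 = 8.15%; difference 7.54 points.

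Here the true 9.24-point difference shrinks.

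**5. Reading the two together.** In step 3 at the 1 vs 0 bound, excluding every control leaver leaves control incidence at exactly 17.65%. The whole shift comes from carrying non-myopic values forward in the treated arm. Step 4 uses no carry-forward and moves against the treatment. The analysis-set rule can therefore distort the comparison in either direction.

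**6. The symmetric case.** If an observation means an outcome examination, and early loss is equal in both arms, unexamined and unrelated to outcome, then 240 down to 204 per arm are analysed for f = 0 to 15%. The expected difference stays at 9.24 points, power falls from 85% to 79%, and type I error stays at 5%.

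**The case against.** A reader might infer that early leavers are kept in the treated arm and lost from the control arm by design. The article does not support that. The weekly visit is for changing adhesives, and no eye measurement is scheduled at it. Table 1 and Outcome observation give both arms the same examinations. The evaluation at withdrawal is open to either arm and follows a request, not a noticed absence. A treated child who leaves before month 3 without an examination is excluded just as a control is. The article also says only that the eye condition is evaluated, so a cycloplegic refraction at exit is not assured. A weekly contact that by itself counted as an observation would create the asymmetry, but nothing in the article says it does.

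Two further inferences also fail. One is that the bias must favour treatment by lowering incidence in the intervention arm alone: step 4 lowers control incidence more and shrinks the effect. The other is that the bias is independent of how missing visits are handled: the spurious benefit in step 3 exists only because of LOCF.

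Finally, requiring a baseline and one later value is a common convention, and the article labels it openly as modified. All of this stands. It does not change the fact that selection occurs after open-label allocation, under contact schedules that differ by arm.

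**Conclusion.** The point holds as a possible bias, not as a demonstrated one. The rule conditions every analysis on a post-allocation event in a trial with unblinded families. Unequal exit examination is plausible, though not fixed by the design, so the groups compared need not be those randomised.

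Under an 80% vs 20% split with LOCF, the spurious benefit is about 0.5–1.6 points, or 6–17% of the planned difference (0.53 / 9.24 to 1.58 / 9.24). The 100% vs 0% figures of 0.9–2.6 points are an outer bound that fits poorly with a withdrawal evaluation open to both arms. Exclusion alone could instead reduce 9.24 points to 8.4–7.5. The early-leaving shares, examination shares and risk ratios behind all these figures are assumptions. The correction is worth making because it is cheap and removes the dependence on who happens to be examined.

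**What to change.** In Statistical analysis:

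- Define the primary set as all randomised children in their assigned arm.
- Replace LOCF with one rule for a missing 12-month outcome, identical in both arms. An example is multiple imputation from baseline spherical equivalent, age, gender, number of myopic parents and any later spherical equivalent.
- Report by arm the number of children with no follow-up.
- Keep the modified set as a sensitivity analysis, stating that an observation means an outcome eye examination in either arm, and align the wording of the Elimination criteria.

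The cost is revised wording and some programming on variables already collected. The interval will be slightly wider, and children with no follow-up will be imputed from baseline variables only, so their contribution rests on the imputation model.

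### Last observation carried forward freezes SE and counts children lost before onset as non-myopic at 12 months, which understates MI and can distort or dilute the arm comparison on both primary outcomes

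*Protocol article*

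**What the plan says.** The Statistical analysis section of the protocol article states: "Last-observation-carried-forward approach will be used to replace missing data". It exempts no outcome. The analysis set is a modified intention-to-treat set that will "involve only subjects who have both a baseline outcome measurement and at least one post-randomization observation".

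Under Primary outcome measures: "The primary outcome measures include MI and SE", and "we define myopia as SE ≤ − 0.50 D". MI status is thus read directly from SE, and a carried-forward SE carries the myopia status with it.

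The MI test is a simple comparison of proportions: "Fisher’s exact test or Pearson’s chi-square test will be used for trial group comparisons of 1-year cumulative MI". SE and the secondary measures are analysed by "Generalized estimating equations (GEE), with one within-subject factor (time), one between-subject factor (intervention), and their interactions". Visits are at 3, 6, 9 and 12 months.

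The Sample size section assumes that cases accrue with time: "The MI in the intervention group 8.41%/year, and that in the control group is 17.65%/year". It allows up to 15% dropout overall and does not split this by arm.

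**The concern.** Carrying a value forward is neutral only if the outcome would have stayed where it was. Here the trial is built on the expectation that it will not: the sample size rests on new myopia appearing through the year. A child last seen non-myopic at month 3, 6 or 9 is counted as non-myopic for the full year, and that child's SE stays at the last value.

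Three consequences follow.

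- MI is understated in each arm that loses children before month 12.
- If acupressure does nothing, the arm that loses more children, or loses them earlier, appears to progress less.
- If acupressure works, equal loss pulls the observed difference towards zero.

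Unequal loss is plausible from the design, though not documented. Intervention families press three times daily and have adhesives changed weekly (Intervention group). Controls attend examinations only (Control group). Families are not blinded (Blinding). Either arm could lose more: one through burden, the other through having been offered nothing.

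**Working it through.** **The plan's own figure.** The Sample size formula with two-sided α = 0.05 and power 0.80:

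n = (1.960 + 0.842)² × [0.0841 × 0.9159 + 0.1765 × 0.8235] / (0.1765 − 0.0841)² = 7.849 × 0.2224 / 0.00854 = 204.4 per group.

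The protocol states 204. Then 408 / 0.85 = 480. The figure reproduces and is not in dispute.

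**Assumptions, none of them in the protocol.** Constant hazard over the year; loss unrelated to outcome; last visit at month 3, 6 or 9 with equal chance; 240 analysed per arm (every child has at least one follow-up visit); linear SE change.

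**MI under LOCF.** Cumulative incidence by month t is 1 − (1 − p)^(t/12). For p = 17.65% this is 4.74%, 9.25% and 13.55% at months 3, 6 and 9, mean 9.18%. For p = 8.41% the mean is 4.28%. With loss L, the LOCF proportion is (1 − L) × p + L × mean.

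*No true effect, 17.65% in both arms:*

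| Loss, intervention vs control | LOCF MI | Spurious benefit | z shift | Type I error |
|---|---|---|---|---|
| 22.5% vs 7.5% (15% overall) | 15.74% vs 17.01% | 1.27 points | 0.376 | 6.6% |
| 20% vs 10% (15% overall) | 15.96% vs 16.80% | 0.85 points | 0.251 | 5.7% |
| 15% vs 15% | 16.38% vs 16.38% | 0 | 0 | 5.0% |

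The z shift is the spurious difference over √[(r(1 − r) + c(1 − c))/240], about 0.0338, where r and c are the two LOCF proportions. Type I error is Φ(−1.96 − z) + 1 − Φ(1.96 − z).

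Equal loss with unequal timing also biases. With 15% lost in both arms, all after month 3 in one and after month 9 in the other, the LOCF proportions are 15.71% and 17.04%, a gap of 1.3 points.

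*Planned effect, equal 15% loss:* intervention 0.85 × 8.41 + 0.15 × 4.28 = 7.79%; control 0.85 × 17.65 + 0.15 × 9.18 = 16.38%. The difference is 8.59 points against the planned 9.24. Power with 240 per arm is about 83%, against about 85% with complete data.

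**SE under LOCF at month 12.** The average time frozen is (9 + 6 + 3)/3 = 6 months. Spurious difference = annual progression × 0.5 × excess loss.

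Progression should agree with the MI the protocol uses. Take baselines spread evenly over the eligible range of −0.5 to +0.5 D (Inclusion criteria) and normally distributed change, and solve for the progression at which 17.65% reach −0.50 D or less. The standard error of the difference is SD × √(2/240).

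| SD of change | Matched progression | Spurious difference at 15 points | Type I error at 15 points | Type I error at 10 points |
|---|---|---|---|---|
| 0.20 D | 0.150 D/year | 0.011 D | 9.5% | 7.0% |
| 0.35 D | 0.069 D/year | 0.005 D | 5.3% | 5.1% |

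So type I error is about 5–10% at 15 points of excess loss and 5–7% at 10 points.

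**The case against.** The strongest reply is that the effect is small where it matters most. MI sizes the trial. At the allowed overall loss its type I error stays below 7%, and equal loss leaves power above the planned 80%. That stands, and it limits the severity.

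Second, the Data collection and management section has children who ask to withdraw examined promptly. This moves the last value later and reduces the bias, but supplies no 12-month value. The Dropout criteria also cover children who do not complete treatment, some of whom may still be examined, so dropout is not the same as a missing month-12 value.

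Third, the SE figures apply to a month-12 contrast. Averaged over the four visits, the frozen time is (0 + 0.083 + 0.25 + 0.5)/4 = 0.21 year rather than 0.5.

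Several stronger readings are tempting and are not supported:

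- *A large SE false-positive rate.* A reader might assume 0.35–0.75 D/year with SD 0.5 D and obtain 9–23% at 15 points of excess loss. Those inputs are not in the protocol and sit badly with its MI. At 0.75 D/year, 31% would become myopic even if every child started at +0.5 D, and 67% with even baselines; 0.35 D/year gives 40% with even baselines. With SD 0.5 D, 17.65% MI allows at most about 0.54 D/year.
- *Bias in the comparison whenever loss differs by arm.* Under the planned effect the arm biases can nearly cancel: loss of 20% versus 10%, all after month 3, gives 9.20 against 9.24 points.
- *Every lost child scored as non-myopic.* Children with no follow-up observation leave the analysis set; the rule affects those seen at least once.
- *Copied visits counted as extra children.* GEE clusters by child and the MI test counts each child once. Copied values are still treated as observed, but the documents do not allow the effect on standard errors to be sized.

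**Conclusion.** The concern holds in limited form. The protocol commits to LOCF for outcomes that it expects to progress, and so understates MI in any arm with loss before onset. With no true effect it favours the arm with more or earlier loss, and with a true effect equal loss dilutes the difference.

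At the protocol's 15% overall dropout, the MI distortion is about 0.8 to 1.3 points for imbalances of 10 to 15 points, against a planned difference of 9.24. The SE results depend on evenly spread baselines and an SD of 0.20–0.35 D; if baselines cluster near +0.5 D, faster progression would fit the same MI and the SE bias would be larger. Loss related to outcome is not covered by these figures.

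This should be fixed, because the error is predictable and cheap to avoid. It does not invalidate the design or the sample size.

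**What to change.** Remove LOCF from the primary analyses, before unblinding.

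- **SE and the other continuous outcomes:** analyse the observed visits under a stated missing-at-random assumption, either in a mixed model for repeated measures (time, arm, their interaction, baseline) or by the planned GEE after multiple imputation. Replacing GEE is optional.
- **MI:** multiply impute SE at missed visits and derive myopia status from it, or use a discrete-time hazard model over the four visits that censors at the last visit. The latter assumes non-informative loss, which should be stated.
- **LOCF:** may remain as a labelled sensitivity analysis.

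The cost is revised analysis wording, a little more programming and possibly slightly wider confidence intervals. No additional children or visits are needed.
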